**Methods**

**Study Design**

A randomised controlled trial would be carried out by recruiting elderly visiting the out-patient-clinic. Subjects will be randomized 1:1:1:1 to receive either computer based cognitive therapy (CBCT) based on a Germen software Rheacom, CBCT+ diet which will be created after modification of Mediterranean diet or CBCT+Diet+ Exercise regime (which will be created by experts in the field of Physiotherapy) and the control group. The intervention group will receive 6 months of intervention to have 40-44 sessions, of 40 minutes duration and the control group brain stimulating activities such as sudoku, mental maths, and learning music and new skills.

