**Outcomes**

The primary outcome will be measured after 6 months by evaluating change in cognitive performance by using PGI Memory Scale total score. Improvements in cognitive domains including executive functioning, processing speed, attention, and memory will be recorded. Secondary outcomes including change in functionality and quality of life will be measured using Barthel's ADL Index, Lawton's Scale, and SF-36 respectively. By utilization of the visual paired associates test, immediate and delayed recall, logical memory immediate and delayed recall, word list learning and delayed recall will be reassessed for noticing changes in the memory domain. Adverse events such as presence of psychological stress, musculoskeletal pain, or injury will be recorded. An external safety committee will regularly assess safety-related issues throughout the duration of the study.

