**Sample Size**

Since it is a pilot study, 15 participants will be recruited in each group as per feasibility. Considering 10% dropout due to loss to follow up, 17 participants will be recruited in to each group giving a total of 68 participants.

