**Analysis Plan**

Data will be entered and analyzed using STATA software. Neuropsychological Test Battery (NTB) total score and the z-scores for executive functioning, processing speed, and memory will be calculated. For computing the NTB total score, at least 8/14 NTB components will be needed; at least 3/5 test scores for the executive functioning domain, 3/6 test scores for the memory domain, and 2/3 test scores for evaluating processing speed. Mixed-model repeated-measures analyses having a maximum likelihood estimation will be used to analyze changes in cognitive performance as a function of randomization group (dichotomous variable coded as 0 for control and 1 for intervention), time (continuous variable coded as 0 for baseline, 6-month visit, characteristic, and group × time × characteristic interaction. The characteristics will be either dichotomous (sex, presence of nutritional risk, and deterioration in quality of life) which will be dichotomized depending on the median value) or continuous variables (age, education level, scores on the following scales: MMSE, Mini-Cog, BADL, IADL, GDS-15, SF-36, and MNA). Log-transformation will be appropriately applied to the skewed continuous variables.

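### The only inference the protocol describes is a set of 12 effect-modifier interactions, not marked as exploratory, in a pilot sized by feasibility at 15 per arm

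*Protocol*

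**What the plan says.** The Sample Size section gives the basis for the numbers: "Since it is a pilot study, 15 participants will be recruited in each group as per feasibility". It then adds an allowance for loss to follow-up: "Considering 10% dropout due to loss to follow up, 17 participants will be recruited in to each group giving a total of 68 participants". No effect size, SD, power or alpha stands behind the 15.

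The Outcomes section names the primary outcome: "The primary outcome will be measured after 6 months by evaluating change in cognitive performance by using PGI Memory Scale total score".

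The Analysis Plan first says what is computed: "Neuropsychological Test Battery (NTB) total score and the z-scores for executive functioning, processing speed, and memory will be calculated". It then describes a mixed model, fitted by maximum likelihood, for changes in cognitive performance. The terms listed are "randomization group (dichotomous variable coded as 0 for control and 1 for intervention"), time, "characteristic, and group × time × characteristic interaction". The characteristics are of two kinds:

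- three dichotomous ones: sex, nutritional risk, and worsening of quality of life;
- nine "continuous variables (age, education level, scores on the following scales: MMSE, Mini-Cog, BADL, IADL, GDS-15, SF-36, and MNA").

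No other inferential analysis is described. The PGI Memory Scale total is not mentioned in that section, and the interactions are not described as exploratory or secondary. MMSE appears only in this list. The assessments under Intervention and Outcomes include Mini-Cog, Barthel, IADL, GDS-15, MNA and SF-36, but not MMSE.

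**The concern.** A pilot of this size can deliver a treatment difference with an honest interval, the SD of change in the primary score, and retention by arm. The Analysis Plan asks for none of these explicitly. It puts its one inferential model on the question of who benefits more, which is the question the sample is least able to answer.

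Two things follow. With this many interaction terms, one or more nominally significant results may well appear when there is no true modification. And with 15 per arm, only a very large true interaction would be detected reliably. A reader shown a significant modifier from this pilot would have no means of telling it from noise, and a later trial could be designed or restricted on the strength of it.

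Two items on the list are also doubtful in themselves. MMSE is not in any assessment described. Worsening of quality of life reads as something observed after randomisation, and quality of life by SF-36 is also a secondary outcome, so it is not a clean baseline modifier.

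**Working it through.** **Inputs from the protocol.** 15 evaluable per arm and 10% dropout (Sample Size); four arms allocated equally (Study Design); a two-level group variable, 3 + 9 = 12 characteristics, and four calculated scores (Analysis Plan). **Assumption:** two-sided alpha of 0.05 per test, because the protocol states none.

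**1. The plan's own figure.** 15 / 0.90 = 16.7, rounded up to 17; 4 × 17 = 68. This reproduces.

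**2. Number of tests.** Taking one characteristic at a time:
- one modelled score: 12 × 1 = 12 tests;
- all four calculated scores: 12 × 4 = 48 tests.

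**3. Expected false positives when no interaction is real** (holds whatever the correlation between tests):
- 12 × 0.05 = 0.6;
- 48 × 0.05 = 2.4.

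**4. Chance of at least one false positive.** If the tests were independent:
- 1 − 0.95^12 = 0.460;
- 1 − 0.95^48 = 0.915.

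They are not independent, so the null case was simulated (1,500 runs per setting). The test was group by characteristic on the 6-month change, which with two visits is equivalent to the three-way term. NTB total was built as a composite of the three domains. Exact-level t-tests were used.

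| Correlation among modifiers / domains | 48 tests | 12 tests on one score |
|---|---|---|
| 0 / 0 | 0.86 to 0.87 | 0.44 to 0.46 |
| 0.3 / 0.5 | 0.73 to 0.76 | 0.37 to 0.40 |
| 0.5 / 0.7 | 0.60 to 0.61 | 0.34 |

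Each range covers 45 v 15 and 15 v 15. Over all settings tried, including 0.2 / 0.3 and 0.5 / 0.5, the 12-test figure ran from 0.32 to 0.46 and the 48-test figure from 0.60 to 0.87. If maximum-likelihood variances are referred to a normal distribution without small-sample correction, the 48-test figure rises to 0.68 to 0.90 (45 v 15) or 0.79 to 0.97 (15 v 15).

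**5. Size of interaction that can be detected.** Take a 50/50 characteristic, in units of the SD of change. The protocol randomises four arms but codes group in two levels, so both readings are given.
- Active arms pooled, 45 v 15: SE = sqrt(2/22.5 + 2/7.5) = 0.596.
- One active arm v control, 15 v 15: SE = sqrt(4/7.5) = 0.730.

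For 80% power, multiply by 1.96 + 0.84 = 2.80:
- 2.80 × 0.596 = 1.67 SD;
- 2.80 × 0.730 = 2.04 SD.

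Power for a given interaction d is Φ(d/SE − 1.96):
- d = 0.8 SD: 0.27 (45 v 15) or 0.19 (15 v 15);
- d = 1.0 SD: 0.39 or 0.28.

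To reach significance at all, the estimate must exceed 1.96 × SE, which is 1.96 × 0.596 = 1.17 SD or 1.96 × 0.730 = 1.43 SD. Any significant interaction of this kind would therefore carry an estimate of more than one SD, whatever the truth.

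**6. MMSE.** Compared with the assessments under Intervention and Outcomes, the other six scales in the continuous list can be matched (BADL to Barthel, IADL to the IADL or Lawton scale). MMSE cannot.

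**The case against.** The strongest defence is that much of this may be settled in a statistical analysis plan that is not shown. Alpha, multiplicity handling and the label given to interaction tests are commonly placed there. That stands: the absence of a multiplicity rule from the protocol is not a fault, and the point does not rest on it.

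Second, a reader might infer that 48 tests are fixed and that a false finding is near certain. The document does not support this. It says four scores will be calculated but does not name the dependent variable of the mixed model. The Outcomes section ties cognitive performance to the PGI Memory Scale total, so one modelled score and 12 tests is a fair reading. One model per characteristic is also an interpretation. The 91% needs independence, and the variables overlap plainly: NTB total with its domains, nutritional risk with MNA, quality of life with SF-36, and MMSE with Mini-Cog.

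Third, a reader might infer that the sponsor intends to claim subgroups that respond, or that nearly every significant modifier will be false. The protocol announces no such claim, and the second statement would need an assumption about how many real modifiers exist. Nor does the text call this analysis primary or rule out reporting estimates and retention.

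Fourth, nine of the 12 characteristics are continuous, so the 50/50 calculation is a benchmark and not a description of every test.

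What remains is what the protocol itself sets down: interaction modelling over 12 characteristics as the only inference described, in a trial it calls a feasibility-sized pilot.

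**Conclusion.** The point holds in a limited form. The described analysis does not match what a pilot of 15 per arm can support, and the interactions are not marked as exploratory. At an assumed two-sided 5% per test, the chance of at least one spurious modifier is about 32% to 46% if one score is modelled (0.6 expected). It is about 60% to 90% if all four are (2.4 expected), and could be higher with uncorrected small-sample tests. Only interactions of about 1.7 to 2.0 SD of change are detectable at 80% power for an evenly split characteristic, so a significant one could not be told from chance.

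These figures rest on the assumed alpha, on testing one characteristic at a time, on 15 evaluable per arm, and on the correlations tried. The conclusion on precision does not depend on how many scores are modelled. The MMSE mismatch stands on its own, subject to MMSE being collected somewhere not described.

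**What to change.** In the Analysis Plan section:

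- State that the pilot reports between-arm differences in 6-month change in PGI Memory Scale total, the primary outcome, as estimates with 95% CIs, together with the SD of change and retention by arm.
- State that interactions with characteristics are exploratory, are limited to characteristics measured at baseline, and are reported as estimates with CIs without significance or subgroup claims. Worsening of quality of life would then leave the list unless it is redefined as a baseline measure.
- Reconcile MMSE: remove it from the list, or add it to the baseline assessments if it is collected.

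A shorter list of modifiers would be a matter of preference and is not required by this point. The change is to wording only. Its downside is fewer subgroup results to report.
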